### 2.3. Sampling method

The sampling method used in this study for the recruitment of participants is by consecutive sampling.

### 2.4. Recruitment of subjects

The source population comprised of male patients diagnosed with alcohol use disorder (AUD) [only male patients are selected as the prevalence of AUD is much higher in men than in women and the majority of patients presenting to the Addiction out-patient clinics are men (5)] registered with the Addiction Outpatient Clinic, Second Affiliated Hospital of Xinxiang Medical University and the Psychiatry Outpatient Clinic, Advanced Medical and Dental Institute, Universiti Sains Malaysia. All potential patients will be approached by the research assistant and provided with brochures that provide information on the research project, the intervention program, duration of the study, and sample collection, as well as a feedback form to enable the research team to identify patients interested to participate in the study. The research assistant will explain the contents of the brochures to the potential patients to ensure that they understand and are clear with the information about the study. Patients who voluntarily agreed to participate in the study will be screened for inclusion and exclusion criteria.

The inclusion criteria are as follows: (1) hospitalized patients diagnosed with alcohol use disorder (confirmed by the relevant diagnostic criteria of Diagnostic and Statistical Manual of Mental Disorders-V); (2) male patients, aged 18–55 years old, Han nationality in China or Malaysian Chinese, junior high school education or above, right-handed (because of the difference in EEG between right-handed and left-handed persons); and (3) those with normal eyesight (including corrected vision). The exclusion criteria are as follows: (1) those with current and lifetime history of abuse of any other psychoactive substances (except tobacco); (2) those with current and lifetime history of mental disorders; (3) those with current and lifetime history of central nervous system diseases or serious medical illnesses; (4) those who are unable to complete the EEG detection or psychological scale assessment; and (5) those who have been administered with psychotherapy or VRET in the past.

Those who are eligible will be offered to participate in the study and explained the objectives and procedures of the study, benefits and risks of participation, their rights to withdraw, anonymity of data collected, data storage, and the incentives, before they signed the informed consent. Consent will be obtained from the research assistant who is not involved in the study. To ensure sufficient participants are recruited for the study, recruitment advertisement regarding the study will be posted in the Second Affiliated Hospital, Xinxiang Medical University and Advanced Medical and Dental Institute, Universiti Sains Malaysia, and the participants will receive an honorarium to compensate for their time spend and travel expenses to participate in this study.

### 2.5. Randomization

The randomization method used for this study is stratified permuted block randomization, in which the trial participants are stratified according to marital status (the strata selected are married, single, and divorced/widower/separated) and monthly income (the strata are <RMB 5,000, RMB 5,000 to RM 10,000, and >RMB 10,000). The participants will be randomized into three groups, such as the VRET group, the ACT group, and the treatment as usual (TAU) group, in a 1:1:1 ratio by a research assistant who is not involved in the study and who is not aware of the study objectives. The randomization is computer generated in which the allocation number is concealed in an opaque envelope that will be given to the participants. Randomization will be carried out by a research assistant who is not involved in the study and does not know the objectives of the study. The research assistant will receive some training on the randomization procedures before the process begins.

#### 2.6.1. Virtual reality exposure therapy

Each session of VRET will last for 25 min and consists of three parts: 5 min of relaxation, 10 min of exposure to high-risk situation, and 10 min of exposure to aversive situation. The relaxation scene includes four beautiful landscapes, and patients can choose any of these four, as perceived to be the most comfortable landscape. The visual stimulation of high-risk scene is designed as any combination of four different scenes (street barbecue stands, restaurant, bar, and home) and four types of alcoholic beverages (Chinese liquor, beer, grape wine, and cocktail), which are customized according to the patient's personal preference. At the same time, the odor of the alcoholic beverage of the patient's choice will be provided as an olfactory stimulation. The aversive situations are visual and auditory stimuli provided by a series of VR videos depicting the harmful effects of alcohol consumption. The VRET session course will be implemented with Oculus Quest VR equipment, whose head screen has a single-eye resolution of 1,600 × 1,440 and field of view of ~100 degrees. It supports the access of left and right dual-channel earphones, providing excellent visual and auditory sensory experience. The VRET manual for this study is presented in Appendix 1.

#### 2.6.2. Acceptance and commitment therapy

The ACT intervention consists of eight sessions, twice a week for 4 weeks. The initial session began with building a therapeutic rapport with the participant and gathering personal information on cognitive fusion, external barrier, unworkable action on alcohol use, experiential avoidance, personal strength, support network, and past life events. Based on the information, a case formulation is constructed. Subsequent sessions involved learning on acceptance and acknowledgment of unpleasant thoughts and feelings associated with alcohol craving and clinical features of alcohol use disorder, cognitive defusion on how to dissociate self-avoidance of unpleasant thoughts and feelings, learning and practicing mindfulness exercise (such as mindfulness breathing) to make self-aware of the many things that occurred presently which can be enjoyed and focus on rather than focusing on unpleasant thoughts and feelings, and learning to be aware of the safe self which is separated from the unpleasant thoughts and feelings and identifying values in life and strategies to achieve these values (therapeutic processes in hexaflex). The ACT manual for this study is included in Appendix 2.

#### 2.6.3. Treatment as usual control

Each participant will receive eight sessions of non-therapeutic activities, such as understanding the psychological indication of treatment, identification of current problems, and opportunity for disclosure and reassurance. The amount of time spend with a professional facilitator for each session is the same as for the other two groups, whereby each session lasted for 1 h and held twice a week for 4 weeks. The participants will be allowed to select either ACT or VRET treatment after the completion of the study.

### 2.7. Treatment fidelity

The ACT sessions will be conducted by four trained therapists who are postgraduate students in psychology and who had experience in conducting psychotherapy for the past 2 years. Initially, these selected postgraduate students will be enrolled in a 2-day workshop on ACT training which is conducted by the principal investigator (PI). Then, they will participate in ACT sessions on alcohol use disorder patients in the out-patient clinic of the PI (from Universiti Sains Malaysia) and co-PI (from Xinxiang Medical University) for 1 month in order to be trained for ACT. For the assessment of the integrity of the ACT sessions conducted, one psychiatrist and one clinical psychologist trained in ACT will conduct the assessments. Then, 15% of the audio-visual recording of the ACT sessions of the four therapists will be randomly selected following stratification with regard to the therapist (first, second, third, and fourth therapists) and the phase of the intervention (early, mid, and late phases of the therapy sessions). The assessment will be performed using the Drexel University CT/ACT Therapist Adherence and Competence Rating Scale (DUACRS) (35). The first assessor will evaluate 50% of the selected recording, and the second assessor will assess another 50% of the recording. Then, the inter-rater reliability between the two assessors will be computed to rate the integrity of the ACT sessions by all the therapists. In addition, any therapists who have any issues while conducting the ACT sessions will discuss their issues with the principal investigator.

### 2.8. Blinding

The researchers will be blinded in this study, in which the recruitment and randomization of the participants will be conducted by a research assistant not involved in this study. The data collection will also be carried out by another research assistant who is also not involved in the study and does not know the objectives of the study. A statistical analysis plan will also be prepared, and the statisticians who will analyze the data are also not part of the research team. The researchers will only be unblinded after the data analysis is completed. The researchers will be unblinded if serious adverse effects occurred in the participant which may or may not be related to the study intervention. The participants are not blinded due to significant differences in the features of the intervention group.

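### The assistant who recruits and takes consent also randomises, in unblinded arms with permuted blocks, and the stated safeguard neither fits the consent process nor prevents prediction of the next arm

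*Protocol article*

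**What the plan says.** Section 2.8 (Blinding) puts two tasks in one role: "the recruitment and randomization of the participants will be conducted by a research assistant not involved in this study". The next sentence separates only the outcome work: "The data collection will also be carried out by another research assistant".

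Section 2.4 (Recruitment of subjects) describes the recruiting task. "All potential patients will be approached by the research assistant", and the same assistant goes through the brochures with them. Eligible patients then have "explained the objectives and procedures of the study, benefits and risks of participation" before they sign. On consent it says: "Consent will be obtained from the research assistant who is not involved in the study" (read here as obtained by the assistant).

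Section 2.5 (Randomization) states the method, "The randomization method used for this study is stratified permuted block randomization", with three marital-status levels and three income levels. It gives two protections. The sequence is computer generated and "the allocation number is concealed in an opaque envelope that will be given to the participants". The other concerns the person: "Randomization will be carried out by a research assistant who is not involved in the study and does not know the objectives of the study".

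Section 2.8 also says that participants are not blinded, because the interventions differ visibly.

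**The concern.** Allocation concealment requires that whoever decides when a patient enters cannot know or infer the next arm. Here one role does both jobs, and the personal safeguard offered is ignorance of the aims. That safeguard has two weaknesses. It sits badly with a consent process in which the aims are explained. It also addresses the wrong thing: prediction from a permuted block needs only a record of earlier assignments, not knowledge of the hypothesis.

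At stake is selection at entry to the comparison of VRET, ACT and TAU on craving. Analysis by intention to treat and the use of outside statisticians do not undo selection that happens before assignment. It would also be hard to detect afterwards. Section 2.9 places the baseline assessment after randomisation, and the primary outcome (PACS, Section 2.9.2.1) is self-administered by unblinded participants, so baseline PACS is not a clean pre-allocation check.

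**Working it through.** **Step 1: who does what.**

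| Task | Who | Section |
|---|---|---|
| Approach patients, explain brochures | The research assistant | 2.4 |
| Explain aims before signature | Not named (passive voice) | 2.4 |
| Obtain consent | The assistant described as outside the study | 2.4 |
| Randomise | An assistant with the same description, unaware of the aims | 2.5 |
| Recruit and randomise | One research assistant role | 2.8 |
| Collect data | A different assistant | 2.8 |
| Generate the list, hold the envelopes | Not stated | 2.5 |

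The union of recruiting and randomising is explicit in Section 2.8. That the same person also takes consent follows from the shared description in Sections 2.4 and 2.5. That this person personally explains the aims is a strong inference, because the assistant covers the brochures and obtains consent, but the text does not say so outright.

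**Step 2: how predictable a block can be.** The plan gives no figure to reproduce.

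*Inputs from the article:* three arms at 1:1:1 (Abstract), 3 × 3 = 9 strata (Section 2.5), N = 120 (Section 2.2), so 120/9 = 13.3 patients per stratum on average.

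*Assumptions:* block size 3, 6, 9 or 12 (none is stated), fixed and known to the guesser; all earlier allocations in the stratum known; complete blocks.

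*Rule:* guess the arm with most places left in the block. At each position the chance of being right is (largest number of places left in any arm) / (all places left), averaged over the possible histories.

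- Block of 3: (1/3 + 1/2 + 1)/3 = 1.8333/3 = 61.1%. Only the last place is certain: 1/3 = 33.3%.
- Block of 6: by position 1/3, 2/5, 1/2, 8/15, 3/5, 1. The sum is 3.3667, and 3.3667/6 = 56.1%. The last place is always certain and the fifth is certain with probability 1/5: 1.2/6 = 20.0%.
- Larger blocks by the same enumeration:

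| Block size | Best guess right | Known with certainty |
|---|---|---|
| 3 | 61.1% | 33.3% |
| 6 | 56.1% | 20.0% |
| 9 | 53.2% | 14.3% |
| 12 | 51.2% | 11.1% |
| Chance | 33.3% | – |

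These are worst-case values. Varying block sizes, incomplete final blocks or partial knowledge of earlier allocations would lower them. They measure predictability only; no effect on PACS follows from them.

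**Step 3: what could be done with a guess.** Table 1 puts eligibility and consent before allocation, and Section 2.6 puts two weeks of in-patient detoxification before random assignment. A guess made at first approach is therefore of little use. One made when several consented patients are waiting could affect which of them is randomised first, or when.

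**The case against.** The other side has four fair arguments.

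- **The sequence is concealed.** Section 2.5 specifies a computer-generated list and an opaque envelope. A reader might infer that the blocks are open, or that the recruiting assistant keeps the envelopes. The article supports neither: the arms are open only after assignment, and no custodian is named. Block size and custody are details that a condensed article may leave to the full protocol, so their absence is not held against the plan. Still, an envelope hides its content from sight, not from inference.
- **Discretion is limited.** Sampling is consecutive (Section 2.3), all potential patients are approached (Section 2.4), and consent precedes allocation (Table 1). This stands, and it confines the risk mainly to the order or timing of randomisation.
- **Past allocations may be only partly visible.** There are two sites in two countries (Section 2.1) and site is not a stratification factor. If the role is filled locally and the strata share one list, an assistant would not automatically know the other site's assignments. This also stands; complete knowledge is an assumption of the worst case.
- **Knowledge of the aims and predictability are separate matters.** Agreed. That is why the safeguard would not protect the sequence even if it held. To call it impossible would go too far, since Section 2.4 does not name who explains the aims.

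None of this removes the stated joining of recruitment and assignment in Section 2.8.

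**Conclusion.** The point holds as a weakness in a stated role assignment. The protocol has one role both enrol and assign, in arms that are visible after assignment and with permuted blocks in nine strata. Its safeguard of ignorance is hard to square with the consent process and does not address prediction.

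The worst-case size is a best guess right about 61%, 56% or 53% of the time for blocks of 3, 6 or 9, against 33% by chance. This rests on a fixed, known block size and full knowledge of earlier allocations in the stratum, neither of which the article establishes.

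A reader might go on to infer that enrolment will be steered or that the craving comparison is biased. The document does not show that: the actual block size, envelope custody and amount of bias are all unknown. The change is worth making because it is cheap and this kind of selection cannot be repaired in the analysis.

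**What to change.** - **Sections 2.5 and 2.8:** state that the assistant who recruits and takes consent neither holds the sequence or envelopes nor assigns the arm.
- **Release of assignments:** have someone already within the plan's structure, but outside recruitment, outcome assessment and outcome analysis, release each assignment once eligibility and consent are logged. A member of the Clinical Trial Coordination Unit (Section 4) could do this, provided that person does not audit this trial, since the unit is its auditor. The list should not go to the statisticians who analyse the outcomes.
- **Blocks:** use varying block sizes that are not disclosed to the sites.
- **Safeguard wording:** for the recruiting assistant, remove the statement about being unaware of the aims, or reconcile it with Section 2.4 by saying who explains the aims and who takes consent.

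The cost is protocol wording, notice of the change to both ethics committees as Section 4 already requires, and one call or email per patient, about 120 in all.

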### 2.9. Measures

This study follows the Standard Protocol Items: Recommendations for Intervention Trials (SPIRIT) 2013. The checklist for SPIRIT is included in Appendix 3. The schedule for assessments in this study is summarized in Table 1. There will be four timelines of assessment. Baseline assessment (t_0_) commences after the randomization of participants into the three intervention groups (VRET, ACT, and control groups), wherein the sociodemographic, clinical, and alcohol use characteristic questionnaire, Alcohol Use Disorder Identification Test (AUDIT), Penn Alcohol Craving Scale (PACS), Hamilton Anxiety Rating Scale (HAM-A), and Hamilton Depression Rating Scale (HAM-D) are administered, while event-related potential (ERP) detection in electroencephalogram (EEG) is performed in the participants. Then, during follow-up assessment, such as t_1_ = 4 weeks (immediately after completion of intervention), t_2_ = 12 weeks (8 weeks after completion of intervention), and t_3_ = 24 weeks (20 weeks after completion of intervention), the questionnaires are re-administered to the participants which include alcohol use characteristics, AUDIT, PACS, HAM-D, and HAM-A, while ERP detection in EEG is re-assessed. The serial assessments will be carried out by a research assistant who is not involved in the research project and does not know about the objectives of the study. The research assistant will receive some training on the administration of the measures before the data collection begins. To ensure that the participants complete the serial assessments and interventions, an appointment card is given to each participant with the next appointment date written on the card. Emails and messages will be distributed 3 days prior to the appointment to remind the participants regarding the appointment date, and if any participant does not reply, a phone call will be made a day before the appointment date.

**Table 1 T1:** Schedule of assessments of the study outcome measures.

	**Enrollment**	**Allocation**	**Post-allocation**		
**Time**	* **–t** _1_ *	***t**_0_* **(0 week)**	* **t** _1_ * **(4 weeks)**	***t**_2_* **(12 weeks)**	* **t** _3_ * **(24 weeks)**

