##### 2.9.3.2. Hamilton Depression Rating Scale

The HAM-D is an observer-administered instrument to assess the severity of depressive symptoms. The HAM-D consists of 21 items but is scored on the first 17 items. The higher the score, the greater the severity of depressive symptoms. The interpretation of the total score is such that the score of 0–7 indicates normal, 8–16 denotes mild depression, 17–23 indicates moderate depression, and 24 and above denotes severe depression (42). The instrument is translated and validated in the Chinese population with an acceptable internal consistency with Cronbach's α of 0.714 (43).

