##### 2.9.3.3. Hamilton Anxiety Rating Scale

The HAM-A is an observer-administered instrument to assess the severity of anxiety symptoms. It consists of 14 items which assess 14 anxiety symptoms. Each item is scored on a Likert scale ranging from 0 (not present) to 4 (severe). A total score of <17 indicates mild severity, 18–24 denotes mild to moderate severity, 25–30 indicates moderate to severe, and >30 indicates severe (44). The instrument is translated and validated in the Chinese population with an excellent internal consistency with Cronbach's α of 0.93 (45).

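### The safeguards stated for the HAM-D and HAM-A rater do not keep the treatment arm from that rater, and the claimed blinding of the researchers is hard to reconcile with the principal investigator's duties

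*Protocol article*

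**What the plan says.** The protocol article calls the trial single-blind. Four parts of it bear on who can know the arm.

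- **Mode of rating.** Section 2.9.3.2: "The HAM-D is an observer-administered instrument to assess the severity of depressive symptoms". Section 2.9.3.3: "The HAM-A is an observer-administered instrument to assess the severity of anxiety symptoms". Sections 2.9.2.1 and 2.9.3.1 describe PACS and AUDIT as self-administered.
- **The rater.** Section 2.9 has the serial assessments "carried out by a research assistant who is not involved in the research project and does not know about the objectives of the study". Section 2.8 says: "The data collection will also be carried out by another research assistant who is also not involved in the study". The word for a second person separates this assistant from the one who recruits and randomizes.
- **The participants.** Section 2.8: "The participants are not blinded due to significant differences in the features of the intervention group". Section 2.5 says that "the allocation number is concealed in an opaque envelope that will be given to the participants". Section 2.9 places the baseline (t0) assessment after randomization.
- **The researchers.** Section 2.8: "The researchers will only be unblinded after the data analysis is completed", with an exception for serious adverse effects. Section 2.7 says that therapists who meet problems while conducting ACT sessions "will discuss their issues with the principal investigator". Section 4 has the principal investigator leading a committee that meets weekly on the daily running of the trial. Section 2.8 also places the analysing statisticians outside the research team.

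**The concern.** Not knowing what a trial is meant to show differs from not knowing what a patient received. A rater may be unaware of the objectives and still learn, in a conversation about mood and anxiety, that the patient has been wearing a headset or attending ACT. HAM-D and HAM-A scores depend on the rater's judgement, so such knowledge can shift them.

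These two scales are two of the four secondary outcomes in Table 1, and they carry the whole of the depression and anxiety objective in section 1.6.2. A difference between arms on them could not be clearly separated from rater expectation.

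The second strand is the accuracy of the blinding statement. A reader of section 2.8 will take it that the research team cannot know who is in which arm before the analysis. The principal investigator's duties elsewhere in the article make that difficult to assure.

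**Working it through.** The point is qualitative and the plan states no figure to reproduce. The check is to ask what each stated safeguard does.

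**Step 1: the rater's safeguards, one by one.**

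| Stated feature | What it prevents | Does it hide the arm? |
|---|---|---|
| Rater is outside the project | Personal stake in the result | No |
| Rater is not the randomizing assistant | Direct sight of the allocation at randomization | Only by that route; the participant can still reveal it |
| Rater is unaware of the objectives | Knowing which arm is hoped to win | No |

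**Step 2: the open route.** The participant is unblinded, is handed the envelope, attends sessions that differ visibly between arms (section 2.6), and is then interviewed by the rater. The t1 visit comes directly after treatment ends. Because t0 follows randomization, the baseline interview is exposed as well, although treatment has not begun. The article states nothing that closes this route.

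**Step 3: reach.** PACS and AUDIT are completed by the participant. Participant expectation can affect them, but the rater's knowledge does not. The rater problem is confined to HAM-D and HAM-A.

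**Step 4: the researchers.** Under section 2.6, ACT is given individually and to one arm only during the trial. A discussion about a particular patient's ACT session therefore places that patient in the ACT arm. Sections 2.7 and 4 together give the principal investigator such discussions and the weekly conduct meetings. No sentence says that allocation is disclosed in either setting, so this step is an inference.

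**Step 5: illustrative size.** Assume no true effect, a rater bias of b standard deviations between two arms, n per arm, and one unadjusted two-sided 5% test. Then

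false-positive rate = Φ(b√(n/2) − 1.96) + Φ(−b√(n/2) − 1.96).

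Section 2.2 gives 40 per arm including 30% dropout, so 40 × 0.7 = 28 would remain. The multipliers are √20 = 4.47 and √14 = 3.74.

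| Assumed bias (SD) | 40 per arm | 28 per arm |
|---|---|---|
| 0.1 | 7.3% | 6.6% |
| 0.2 | 14.5% | 11.6% |
| 0.3 | 26.9% | 20.2% |
| 0.4 | 43.2% | 32.2% |

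The bias values are assumptions with no source in the documents. The test is also not the planned one: section 2.10 plans a three-group mixed ANOVA interaction, plus one-way ANOVAs with false discovery rate adjustment. In the interaction test, a bias that is constant over all four visits would fall into the group effect, whereas one that changes between visits would enter the interaction.

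**The case against.** The best defence is that this is a condensed article. Operating details such as room separation, access to schedules and non-disclosure scripts usually sit in the full protocol. The assistant's independence is described under the Blinding heading of a single-blind trial with unblinded participants, so blinded assessment is probably intended. The rater is also kept apart from randomization, which is a genuine protection.

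Much of this stands. A reader might infer that the rater knows the arm; the documents do not say so. A reader might also infer that ignorance of the objectives is the sole safeguard, and section 2.8 shows that it is not. What the defence does not answer is that the article states its mechanism twice, and that the mechanism, followed exactly, leaves the arm discoverable. That is more than omitted detail.

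On the principal investigator, a reader might go further and say that the article shows the role to be unblinded. It does not. The ACT training in section 2.7 is a preparatory workshop followed by a month of sessions on clinic patients, and it reveals no trial participant's arm. Participants carry research numbers, therapists' problems can be discussed without naming a patient, and nothing says that the weekly committee sees allocations. The principal investigator is also not described as collecting outcomes, and the statisticians are external, so no direct path to a biased result is shown. What remains is that the assurance in section 2.8 is hard to square with these duties.

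Finally, the false-positive rates could be mistaken for an estimate of this trial's error. They are not, for the reasons given with the table.

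**Conclusion.** The point holds within limits. As written, the safeguards do not keep the arm from the HAM-D and HAM-A rater, so two of four secondary outcomes, including their t0 values, are open to rater expectation bias. The primary outcome PACS and the AUDIT are outside the reach of this problem. That conclusion rests on the article's own description of the rater, the participants and the timing of baseline, and needs no numerical assumption.

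Whether bias would occur, and how large it would be, cannot be known from the documents. The range of about 7% to 43% at 40 per arm (7% to 32% at 28 per arm) depends entirely on assumed biases of 0.1 to 0.4 SD and a simplified test, and should be either labelled as illustrative or left out.

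The statement on researcher blinding is a lesser matter: a risk inferred from the principal investigator's roles, which calls for clearer wording. Overall this is something the sponsor should correct, but it does not threaten the primary comparison.

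**What to change.** In sections 2.8 and 2.9:

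1. State that the HAM-D and HAM-A rater is kept unaware of allocation, with no access to envelopes, session schedules or session records.
2. Have participants told before each visit, t0 included because it follows randomization, not to mention their treatment to the rater.
3. Record any disclosure, and the rater's guess of the arm, at t1, t2 and t3, so that the success of masking can be reported.
4. Replace the general statement on researchers with a list by role: raters and statisticians blinded; participants and therapists not blinded; the principal investigator not assured to be blinded, given the supervision and monitoring duties.

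The cost is a few sentences of protocol wording, a short script and one extra field on the form. The same assistant continues to do the ratings, so no extra staff are needed.
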